### Sample size

The sample size was estimated using G*Power software (version 3.1.9.7, Franz Faul, Universität Kiel, Germany). The primary outcome is the KOOS₄ score (mean score of the Pain, Symptoms, Activities of Daily Living, and Knee-Related Quality of Life subscales) from the Knee Osteoarthritis Outcome Score (KOOS). Based on previous research, a 10-point improvement in KOOS₄ was considered the Minimum Clinically Important Difference (MCID), with an anticipated Standard Deviation (SD) of 15 points [41, 42]. The following parameters were utilized for the sample size calculation: Significance Level (α) = 0.05, Statistical Power (1-β) = 0.90, Effect Size (Cohen's f) = 0.34, and Number of Groups = 4. The calculations indicated that the minimum total sample size required to detect this effect was 128 cases. Considering an anticipated attrition rate of approximately 15% and to ensure equal and balanced allocation across four groups, the total sample size was increased to 148 participants, resulting in 37 participants per group. This approach enhances the stability and reliability of the study results, ensuring that the research objectives will be successfully met.

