### Statistical analysis

All statistical analyses will be conducted using SPSS version 27.0 (IBM Corp., Armonk, NY, USA) by statisticians blinded to group allocation. All tests will be two-tailed with a significance level set at *P* < 0.05. Baseline characteristics will be summarized using descriptive statistics. Continuous variables will be presented as mean ± standard deviation (SD) or median (interquartile range), depending on data distribution. Categorical variables will be expressed as frequencies and percentages. All efficacy analyses will follow the intention-to-treat (ITT) principle. The primary analysis will focus on evaluating whether the longitudinal response trajectory of the combined PNE + BFRT group differs from those of the comparison groups over time. To address this objective, linear mixed-effects models (LMMs) will be used for repeated-measures analyses of the primary and secondary outcomes. The primary inference of interest will be based on the group-by-time interaction effect, which reflects differential changes in outcome trajectories between intervention groups throughout the study period. To reduce the risk of type I error inflation, KOOS₄ will be considered the sole confirmatory primary outcome, while all other outcomes will be treated as secondary or exploratory. If a significant group-by-time interaction is identified for KOOS₄, post-hoc pairwise comparisons with Bonferroni correction will be performed. Secondary outcomes will be analyzed using similar mixed-effects modeling approaches. Estimated marginal mean differences with 95% confidence intervals will be reported where appropriate. Missing data will be assumed to be missing at random and handled using maximum likelihood estimation within the mixed-effects modeling framework. A supplementary per-protocol analysis, including participants with at least 80% adherence to the intervention, may also be conducted.

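### 148 randomised less the stated 15% attrition leaves about 126 completers, just under the plan's own minimum of 128; 148 covers about 13.5%

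*Protocol article*

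**What the plan says.** All the figures stand in one paragraph, under Sample size in the protocol article.

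- The calculation inputs are "Significance Level (α) = 0.05", "Statistical Power (1-β) = 0.90", "Effect Size (Cohen's f) = 0.34" and four groups.
- The result is that the "minimum total sample size required to detect this effect was 128 cases".
- The allowance for loss is worded "Considering an anticipated attrition rate of approximately 15" per cent, and equal allocation across the arms is given as a second reason for the increase.
- The outcome is that "the total sample size was increased to 148 participants, resulting in 37 participants per group".

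The paragraph does not print the formula that leads from 128 to 148. It closes by saying that this approach secures the aims of the study.

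Two other sections bear on the point. Statistical analysis plans intention-to-treat linear mixed-effects models, with missing data handled by maximum likelihood under a missing-at-random assumption. The Discussion names dropout over the long follow-up as a risk to power.

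**The concern.** An attrition rate is a share of those randomised. If 128 is the minimum and 15% are expected to leave, the number randomised has to be large enough that 85% of it is at least 128. The stated 148 does not meet that condition.

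The figure is what one gets by adding 15% to 128, a common slip, instead of dividing 128 by 0.85. What is at stake is the internal consistency of the sample size statement. The paragraph calls 128 a minimum and then sets a total that does not deliver it at the loss rate given alongside it. The allowance is also the design's only numerical protection against the dropout risk that the Discussion acknowledges.

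**Working it through.** **Inputs, all from the Sample size section:** α = 0.05; target power 0.90; Cohen's f = 0.34; 4 groups; minimum total 128 (32 per group); attrition about 15%; total randomised 148 (37 per group).

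**Step 1: reproduce 128.** Use the omnibus F test of a one-way fixed-effects ANOVA with k = 4 groups. Under the alternative, F is noncentral with df 3 and N − 4 and noncentrality λ = N × f². Power is the probability that it exceeds the 0.95 quantile of the central F. The smallest N with power of at least 0.90 is 127, or 128 as a multiple of four. The plan's 128 is reproduced.

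**Step 2: reproduce 148.** 128 × 1.15 = 147.2, rounded up to 148, which divides by four. This matches the stated total, but the multiplier is inferred because no formula is printed.

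**Step 3: apply the stated loss to 148.** 148 × 0.85 = 125.8, about 126, or 37 × 0.85 = 31.45 per arm against 32. This step does not depend on how 148 was obtained.

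**Step 4: the total that would retain 128.** 128/0.85 = 150.6, so 151, or 152 (38 per arm) for equal arms. Check: 152 × 0.85 = 129.2, which is at least 128. The difference from the plan is 152 − 148 = 4 participants.

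**Step 5: the loss that 148 does cover.** (148 − 128)/148 = 20/148 = 13.5%.

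**Step 6: effect on power, same F calculation, f = 0.34.**

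| N | λ = N × 0.34² | Power |
|---|---|---|
| 128 | 14.80 | 0.9036 |
| 127 | 14.68 | 0.9011 |
| 126 | 14.57 | 0.8985 |

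Going from 128 to 126 costs 0.9036 − 0.8985 = 0.0051 in power. Against the target itself the gap is 0.90 − 0.8985 = 0.0015.

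**The case against.** The strongest reply is that nothing of substance is lost, and most of it stands.

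- **The rate is approximate.** The text says approximately 15%, and 148 covers 13.5%, a gap of 1.5 percentage points. This softens the point but does not remove it: a reader who takes the printed rate at face value arrives at 126, not 128.
- **The power target is met to the precision stated.** With 126 completers power is 0.8985, which is 0.90 to two decimals. The unrounded minimum is 127, so the shortfall against the target is about one participant. This stands in full.
- **The mixed model keeps partial data.** Under maximum likelihood, a participant who leaves after some follow-up visits still contributes the visits already made. This stands too, and it makes the effective loss smaller than a count of completers suggests. The Sample size section does not rely on this argument, however, so it does not reconcile the printed figures.

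A reader might be tempted to infer more than the article supports, in four ways:

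- *That a wrong formula was used.* The fit to 128 × 1.15 is exact after rounding, but the article does not state its method and also cites equal allocation. Only the mismatch of the figures is established.
- *That only 126 will be analysed.* That would describe a completers analysis. The planned analysis is intention-to-treat with maximum likelihood, so 126 is the number expected to complete follow-up.
- *That the count falls to 124, at 31 per arm.* This needs a further rounding down in every arm, which does not follow from 148 × 0.85 = 125.8.
- *That the trial is materially underpowered because of this.* A loss of 0.0051 in power does not support that.

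**Conclusion.** The point holds as a minor inconsistency. The stated total of 148, less the stated 15%, leaves about 126 completers and so does not deliver the stated minimum of 128. The size is two completers, or four randomised participants when set against the consistent total of 152. Power on the plan's own calculation is 0.8985 instead of 0.9036.

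The shortfall itself is arithmetic on printed figures; it requires only that 15% is read as the share of randomised participants lost. The power figures rest on f = 0.34 taken as given and on the one-way F test that reproduces 128. They say nothing about power for the group-by-time interaction in the planned mixed model. No design or analysis decision changes, but the sentence should be corrected because its figures contradict each other.

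**What to change.** Keep 148 and restate one figure in the Sample size paragraph. Either wording is sufficient:

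- *The total of 148 (37 per group) allows for about 13.5% attrition (20 of 148) while retaining 128 participants.*
- *With 15% attrition, about 126 of the 148 participants complete follow-up, and power is about 0.90 (0.8985) on the stated assumptions.*

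In the second form, write that they complete follow-up and not that they are analysed, so that the sentence agrees with the Statistical analysis section. Either form costs one sentence and no extra participants.

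If the sponsor prefers to keep both 15% attrition and 128 completers, the consistent total is 152 (38 per arm). That means four more participants, and the total would have to be changed wherever 148 appears (Abstract, Study design and Sample size), with the amendment submitted to the Ethics Committee and the registry as the article already provides. Given the size of the effect, restating the figure is the proportionate choice.

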### Interventions

#### The control group

Participants allocated to the Control group will continue receiving their ongoing conservative management for persistent pain after TKA, including stable medication use, self-directed physical activity or exercise, and routine medical care when necessary. No structured PNE or supervised exercise intervention will be provided during the study period.

#### The PNE group

Participants allocated to the PNE group will additionally receive two one-hour PNE sessions delivered by a licensed physical therapist with formal training in pain neuroscience education [28]. The primary goal of PNE is to alter maladaptive pain cognitions, helping participants to reconceptualize their pain and enabling them to better self-manage their symptoms [43]. The first session (Week 0) will introduce core concepts of pain neuroscience, including peripheral and central sensitization, hyperalgesia, and the distinction between tissue damage and pain perception. Mechanisms underlying CPSP following TKA will be explained using patient-centered language and visual aids. The second session (Week 6) will reinforce previously introduced concepts, address participants’ pain-related questions, facilitate discussion of pain management experiences, and further strengthen participants' cognitive understanding and coping abilities regarding their own pain. Participants will receive a concise information booklet summarizing the PNE topics. The detailed curriculum and learning objectives for each session are outlined in Supplementary Appendix 1. Attendance at both PNE sessions is considered complete adherence to the core intervention, whereas attendance at only one session is considered partial adherence and failure to attend either session is considered non-adherence.

#### The BFRT group

Participants in the BFRT group will additionally undergo a 12-week supervised BFRT program conducted twice weekly for a total of 24 sessions [28, 44]. Before the intervention, participants will complete three familiarization sessions separated by at least 48 h to standardize exercise technique and minimize learning effects [45]. The individualized Arterial Occlusion Pressure (AOP) will be determined using a Doppler ultrasound probe (DV-600; Marted, Brazil) in the supine position [44]. Detailed procedures for AOP measurement are provided in Supplementary Appendix 2. The training intensity will be anchored to the participant's 1-repetition maximum (1-RM) for leg press and knee extension exercises assessed using standard resistance equipment (Nakagym, São Paulo, Brazil). The 1-RM assessment protocol is detailed in Supplementary Appendix 3 [44, 46]. The intervention will follow a progressive overload model. The first week served as an adaptation phase, employing a training intensity of 20% 1-RM, completed in 4 sets of 15 repetitions each. Starting from Week 2, the training intensity was increased to 30% 1-RM, and from Week 5, the number of sets per training session was increased to 5. Inter-set rest intervals will be standardized at 1 min. During training, cuff pressure will be set at 70% of the individualized AOP, and the cuff will be inflated immediately before the first set and deflated after completion of the final set [44].

To maintain training load stability and ensure BFRT efficacy, both the 1-RM and AOP will be reassessed every 4 weeks to adjust training loads and cuff pressure based on updated values. Throughout the intervention, adverse events and participant discomfort will be continuously monitored.

#### The combined intervention group (PNE + BFRT)

In addition, participants allocated to the combined intervention group will receive both PNE and BFRT according to the same protocols described above. PNE sessions will be delivered at Weeks 0 and 6, while BFRT will be conducted twice weekly throughout the 12 weeks. On weeks when both interventions occur, PNE sessions will precede exercise training to avoid fatigue-related interference.

Participants in all groups will be instructed to maintain their existing medications and conservative management strategies throughout the study period whenever possible.

Any concomitant treatments, including analgesic use, physiotherapy, injections, or additional rehabilitation interventions, will be recorded during follow-up.

### Outcomes

Patients with CPSP following TKA often experience not only pain but also difficulties with activities of daily living (ADL). Since our goal is to both alleviate pain and improve physical function, we have selected the following measures as outcome indicators. Outcome assessments will be conducted at baseline, post-intervention (12 weeks), and follow-up at 24, 36, and 48 weeks [28].

### Primary outcome

#### KOOS_4_

The primary outcome is the between-group difference in longitudinal change in KOOS₄ across all assessment time points. KOOS_4_ was selected as the primary outcome measure because persistent CPSP after TKA affects not only pain intensity but also broader dimensions of knee-related symptoms, activities of daily living, and quality of life, making patient-centered assessment essential when evaluating treatment outcomes. It is one of the most widely used and validated assessment tools in patients undergoing TKA [28].

The KOOS₄ is calculated as the mean of four KOOS subscales (Pain, Symptoms, Activities of Daily Living, and Knee-Related Quality of Life), excluding the Sport/Recreation subscale. Scores range from 0 to 100, with higher scores indicating better knee-related function [47, 48]. Based on prior literature, A between-group difference of 10 points is considered the MCID and will be used to interpret the clinical relevance of observed effects [42].

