**Methods and analysis:**

This study is a single-blind, four-arm, parallel-group randomized controlled trial. A total of 148 participants will be randomly assigned (1:1:1:1) to the Control, PNE, BFRT, or combined PNE + BFRT group. PNE will be delivered in two structured sessions. BFRT involves a 12-week supervised low-load resistance training program. The primary outcome is the group-by-time interaction effect on KOOS₄ over time. Secondary outcomes include pain intensity (NRS), global perceived effect, pain distribution, psychological measures (HADS, PCS), physical performance (40-m fast-paced walk test, stair climb test, and 30-s chair stand test), and neuromuscular strength. Assessments will be conducted at baseline, post-intervention (12 weeks), and at 12-week, 24-week, and 36-week follow-ups. Data will be analyzed using linear mixed-effects models under the intention-to-treat principle.

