## Method and analysis

### Study design

The study is designed as a single-center, four-arm, parallel-group, superiority randomized controlled trial. A total of 148 participants will be recruited from the Chengdu Sport University. All therapeutic interventions and data collection will be conducted at the School of Sports Medicine and Health, Chengdu Sport University.

Potential participants will be targeting individuals who underwent unilateral TKA at least one year prior. Eligible candidates will be contacted by telephone for preliminary screening. Those meeting eligibility criteria will be invited for an in-person baseline assessment and receive a comprehensive explanation of the study procedures. Written informed consent will be obtained before enrollment. A screening log will be maintained to document eligibility and reasons for exclusion. Participants will be consecutively recruited until the required sample size (n = 148) is achieved. Participants will be randomly assigned in a 1:1:1:1 ratio to one of four groups: the Control group, the PNE group, the BFRT group, or the PNE combined with BFRT group.

The study has received approval from the Ethics Committee of the Chengdu Sport University (Committee Reference Number: CDSUEC2026- 177) and is registered with the Chinese Clinical Trial Registry (Registration Number: ChiCTR2600125544). The trial will be conducted in accordance with the Declaration of Helsinki. Any protocol amendments will be promptly submitted to the Ethics Committee and updated in the trial registry. Given the low-risk nature of the interventions, an independent data monitoring committee will not be established. However, all adverse events will be recorded and monitored throughout the trial. Any serious adverse events (SAEs) will be immediately reported to the Ethics Committee.

The study period will span from May 2026 to July 2029. Participant recruitment will occur between May 2026 and July 2027. Follow-up assessments will be completed by July 2029. The study protocol was developed in accordance with the SPIRIT 2025 Statement, as shown in Fig. 1. The timeline for participant enrollment, interventions, assessments, and follow-up visits is detailed in Table 1.

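### The confirmatory KOOS₄ result is an omnibus group-by-time interaction over five assessments, so no single estimate or visit carries the superiority claim or the 10-point MCID

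*Protocol article*

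**What the plan says.** The Abstract gives the primary outcome as an interaction: "The primary outcome is the group-by-time interaction effect on KOOS₄ over time". The KOOS₄ section under Primary outcome words it as "The primary outcome is the between-group difference in longitudinal change in KOOS₄ across all assessment time points". The Statistical analysis section agrees: "The primary inference of interest will be based on the group-by-time interaction effect". It makes KOOS₄ the only confirmatory outcome, with two-sided tests at 0.05.

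The Outcomes section fixes five assessments: "Outcome assessments will be conducted at baseline, post-intervention (12 weeks), and follow-up at 24, 36, and 48 weeks".

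The follow-up step is "If a significant group-by-time interaction is identified for KOOS₄, post-hoc pairwise comparisons with Bonferroni correction will be performed". That sentence names no visit.

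The KOOS₄ section adds a benchmark: "A between-group difference of 10 points is considered the MCID and will be used to interpret the clinical relevance of observed effects". No visit is attached to it there or in the Sample size section. The design is a "four-arm, parallel-group, superiority randomized controlled trial". The hypothesis at the end of the Introduction, that the combined arm does better than each of the other three, also carries no time point. Nowhere does the article rank the visits or define an average over them.

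**The concern.** An interaction test asks whether four trajectories are parallel. Rejecting it says that they are not, somewhere. It does not say whether the benefit is present at the end of treatment, arises later, persists or fades, and it does not say which arm is better. A superiority trial with a 10-point benchmark needs a number to set against that benchmark, and the stated primary result does not produce one.

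The claim must then come from pairwise comparisons. Six arm pairs at four post-baseline visits give 6 × 4 = 24 candidates, and the visits can disagree. Two readers of the same data could reach opposite conclusions, one from Week 12 and one from Week 48, and both could cite the plan.

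**Working it through.** **The plan's own figure.** One-way ANOVA with four groups, f = 0.34, α = 0.05 and power 0.90: at N = 128 the noncentrality is N·f² = 128 × 0.1156 = 14.8, and power is 90.4%. The stated 128 (32 per arm) reproduces. It is a calculation for one measurement per patient, and it too names no visit.

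**Inputs.** From the Sample size section: 32 per arm, SD σ = 15, difference 10 points. From the Outcomes section: five visits. Assumed, because the article does not give them: time as a category, equal within-person correlation ρ (0.5, range 0.3 to 0.7), known variance, no missing data.

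**Degrees of freedom.** (4 − 1) × (5 − 1) = 12.

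**Power of the interaction.** Let only the combined arm differ, with benefit v = (v₁, …, v₄) at Weeks 12, 24, 36 and 48. The noncentrality is

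λ = n × 0.75 × [Σv² − (Σv)²/5] / [σ²(1 − ρ)].

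At ρ = 0.5 the denominator is 225 × 0.5 = 112.5, and n × 0.75 = 24.

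- Week 12 only (10, 0, 0, 0): 100 − 100/5 = 80; λ = 24 × 80/112.5 = 17.07; power 79%.
- All four visits (10, 10, 10, 10): 400 − 1600/5 = 80; λ = 17.07; power 79%.
- Week 48 only: again 80, 79%.

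The bracket is identical, so the equality holds at any ρ: 61% at 0.3 and 97% at 0.7. Under these assumptions the test responds equally to a transient, a late and a lasting benefit.

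**Power of a named contrast.** These are 3-df tests across the four arms at ρ = 0.5. A single visit has change variance 2σ²(1 − ρ) = 225, so a 10-point benefit gives λ = 24 × 100/225 = 10.67. The mean change over Weeks 12 to 48 has variance σ²(1 − ρ)(1 + 1/4) = 140.6, so a 10-point mean gives λ = 24 × 100/140.6 = 17.07 and a 5-point mean gives 4.27.

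| Benefit at Weeks 12, 24, 36, 48 | Interaction | Week 12 | Mean of Weeks 12–48 |
|---|---|---|---|
| 10, 10, 10, 10 | 79% | 79% | 95% |
| 10, 7, 3, 0 | 78% | 79% | 38% |
| 0, 3, 7, 10 | 78% | 5% | 38% |

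**Error rate of the follow-up tests (conditional).** Simulation on change from baseline, 32 per arm, with the interaction as gate:

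- All arms equal, divisor 3 or 6 reused at each visit: 3.0% to 3.6% false claims.
- Only Control differs (three active arms equal, each 10 points better), divisor 6 reused at each of four visits: 6.9%, 7.6% and 7.9% at ρ = 0.3, 0.5 and 0.7; about 7.7% once the gate is open. Counting only combined versus PNE or BFRT, about 5.5%.
- The same situation with divisor 24: 2.0% to 2.2%.

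**The case against.** The strongest reply is that nothing is left open. There is one confirmatory outcome, one model and one two-sided test, stated consistently in three places, and the declared question is whether trajectories differ. An omnibus trajectory test is legitimate. This stands as far as it goes: a reader might infer that the primary test is not pre-specified, and the article does not support that. What the test lacks is an estimate and a direction for a superiority claim.

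A second reply is that time coding, the list of post-hoc pairs and the Bonferroni divisor belong in an analysis plan that is not shown. That also stands, and their absence is not the point here. The definition over all time points is what the article itself fixes; a deciding visit in an analysis plan would change it.

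A third reply concerns the remedy. Naming Week 12 would not stop a fading benefit from being declared positive (79% against 78% for the interaction); it only makes plain what was shown. Nor is a named visit free: that reading holds only when the full benefit is already present at Week 12. The contrast powers above are also 3-df tests across arms. For one directional comparison of the combined arm with another arm at 0.05/3 (10 points, SD 15), power is 61% at 32 per arm and 68% at 37. All of this stands and belongs with the fix.

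A reader might finally infer that the plan inflates the type I error in general. It does not: with all arms equal the gate keeps the rate below 5%. The excess needs a divisor that ignores visits, which the article does not state, and a true difference in some arm.

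**Conclusion.** The point holds as a weakness in how the primary result is defined. It should be corrected, but it does not invalidate the trial. The interaction cannot say when or in which direction the combined arm differs, and the MCID has no estimate to be judged on. The equal power for a Week 12-only and a sustained benefit (79% each) assumes categorical time, equal within-person correlation, 32 per arm and SD 15. The level moves between 61% and 97% over correlations 0.3 to 0.7; the equality does not. The absence of a deciding contrast depends on none of these assumptions. The error-rate point is conditional only, and it disappears if the correction counts visits as well as arm pairs.

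**What to change.** In the KOOS₄ and Statistical analysis sections, name one time contrast from the same mixed model as the confirmatory KOOS₄ quantity: either change from baseline to Week 12, or mean change over Weeks 12 to 48. Judge the 10-point MCID on that contrast. Keep the interaction as a supportive description of the trajectories. Treat the remaining visits as secondary, or test them in a stated fixed order afterwards.

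If visit-wise pairwise tests are kept instead, apply Bonferroni over arm pairs and visits together (24 if all six pairs are tested at four visits).

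The cost is a few sentences, an ethics amendment and a registry update, for which the Study design section already provides; no new data or patients are needed for the change itself. The choice should be made on the pattern the sponsor expects and its downside stated. Week 12 misses a late benefit, and under a fixed order a failure there also blocks the later visits. The average loses power if the benefit fades or comes late and gains if it lasts. The sample size should be rechecked against the chosen contrast.
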